### Economic analysis

We will establish the cost-effectiveness of CfD compared to CBT [59]. The purpose is to establish what the additional benefit and resource implications of CfD are relative to CBT. The primary analysis will be from a health and social care perspective and will therefore include costs to the NHS and social care services. The method used to conduct this economic analysis will depend on treatment outcomes.

Where treatment outcomes are found to be equivalent based on the primary measure of efficacy, a cost minimisation analysis will be conducted. In this case, the focus will be in assessing any cost differences between CfD and CBT.

Total costs of each intervention will be estimated using the number of sessions multiplied by national unit costs and data from the local Trust. The consequences for the use of other health and social care resources (including hospital admissions, outpatient attendance, GP visits, other therapy and medication) will be measured using a patient-completed resource use questionnaire and service data and costed with national unit costs. Individual level mean costs (intervention and other resource use) for CfD and CBT will be compared; uncertainty around the costs estimates will be generated using probability sensitivity analysis. One-way sensitivity analysis will be conducted on key assumptions such as the number of sessions.

Where one intervention proves to be more effective, then a cost-effectiveness analysis (CEA) will be undertaken using the estimated incremental cost per quality adjusted life year (QALY), that is, the difference in outcomes divided by the difference in costs for CfD and CBT. The primary outcome measure for the CEA will be the EQ-5D-5L. The EQ-5D-5L is a generic preference-based measure of health designed for calculating QALYs. It is composed of five dimensions: mobility, self-care, usual activities, pain/discomfort and anxiety/depression, each with five levels describing 3125 health states in total. The EQ-5D-5L is a revision of the EQ-5D, the NICE recommended measure for economic evaluation, offering better sensitivity [46]. The EQ-5D-5L has been valued by the general public in England and we will apply these new values to generate utility values [60]. QALYs will be estimated from the EQ-5D-5L collected from patients at baseline, 6 and 12 months. Individual patient level data on costs and QALYs over 12 months will be used to estimate the mean cost-effectiveness of CfD compared to CBT and the underlying uncertainty around it by a probabilistic sensitivity analysis.

One-way analysis of key assumptions will be undertaken and where differences persist at 12 months then the analysis will be extrapolated beyond 12 months. Additional analysis will include assessing outcomes for CfD compared to CBT in terms of the proportion who achieve reliable and clinically significant improvement based on the PHQ-9 [56, 57]. Patients will be classified as having had a reliable and clinically significant improvement if they change by 6 points *and* move from a clinical population at baseline (10 and above) to a non-clinical population (9 or less) at 12 months. This will be combined with incremental costs to establish the incremental costs associated with reliable and clinically significant improvements.

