### Primary analysis

The primary analysis will adhere to a Statistical Analysis Plan (SAP) devised by an independent statistician under the guidance of the senior medical statistician. The SAP was informed by the International Conference on Harmonisation topic E9 [53], reference to the literature (e.g., [54]) and applicable standard operating procedures from the University of Sheffield Clinical Trials Research Unit (CTRU). Non-inferiority of counselling to CBT will be concluded if the CI lies entirely above the non-inferiority limit of −2 units (i.e., that a difference as large as 2 units in favour of CBT has been ruled out).

In contrast to superiority trials, the ITT analysis is anti-conservative (i.e., it underestimates the treatment effect) when looking at non-inferiority. Specifically, if an intervention is not delivered as fully planned by the protocol the ITT analysis dilutes the treatment difference and therefore raises the risk of having the groups look artificially similar (and hence CfD being artificially non-inferior to CBT). Given the pragmatic nature of the trial the ITT will remain the primary analysis population, but additional consideration will be given to other analyses that exclude participants who did not receive the intervention as planned. It should also be noted there is a general lack of guidance regarding the choice of the primary analysis population for non-inferiority trials [55].

The additional analysis populations are:An objective per-protocol analysis (PP1) that excludes participants who receive fewer than four sessions within 6 months of randomisation and/or who switch treatment arms within 6 months of randomisation.A case-review per-protocol analysis (PP2) in which participants are assessed on a case-by-case basis for the number and timing of sessions, additional therapies received and therapist adherence to principles of CBT or CfD. This will necessarily be unblind to treatment group but will be blind to outcome data.Complier-adjusted causal effect (CACE) models in which participants who undergo their intervention in accordance with protocol are compared to those in the comparator group who are “likely” to have done so (based on statistical modelling) had they been randomised to receive it. Two CACE analyses will be undertaken, one of which excludes “non-receivers” of CBT and the second removing “non-receivers” of CfD.

A fuller description of these analyses is provided in the Statistical Analysis Plan.

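### The economic method is chosen from the PHQ-9 result, but a one-sided non-inferiority test cannot show equivalence, and the cost-minimisation branch leaves the QALY difference out of the economic result

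*Protocol article*

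**What the plan says.** The Economic analysis section makes the method conditional: "The method used to conduct this economic analysis will depend on treatment outcomes". It then gives two branches.

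- **Cost minimisation.** "Where treatment outcomes are found to be equivalent based on the primary measure of efficacy, a cost minimisation analysis will be conducted". Its content is limited to costs: "In this case, the focus will be in assessing any cost differences between CfD and CBT". The uncertainty described is also limited to costs: "uncertainty around the costs estimates will be generated using probability sensitivity analysis".
- **Cost per QALY.** "Where one intervention proves to be more effective, then a cost-effectiveness analysis (CEA) will be undertaken". Here "The primary outcome measure for the CEA will be the EQ-5D-5L", and "Individual patient level data on costs and QALYs over 12 months will be used to estimate the mean cost-effectiveness", with probabilistic sensitivity analysis.

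The switch rests on the primary efficacy measure, the PHQ-9. According to the Primary analysis section, success there means "that a difference as large as 2 units in favour of CBT has been ruled out". The Sample Size section sets a single margin, in the direction favouring CBT, tested one-sided at 2.5%. Cost-effectiveness is part of the primary objective (Objectives).

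**The concern.** Three things do not fit together.

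1. The first branch needs a finding of equivalence. The design has one limit, no upper limit and no equivalence test, so the planned primary analysis cannot return that finding.
2. Even a clear non-inferiority result concerns the PHQ-9, with the sample size built on 6-month follow-up. The QALY comes from a different instrument, the EQ-5D-5L, accumulated over 12 months. A PHQ-9 deficit shown to be smaller than 2 points does not make the QALY difference zero, yet a costs-only analysis treats it as zero and known without error.
3. The two branches do not cover every result. A confidence interval containing both −2 and 0 shows neither non-inferiority nor an advantage for either arm.

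At stake is the economic half of the primary objective. A costs-only result can make the cheaper arm look preferable with less uncertainty than the trial's data support. It also cannot deliver what the section sets as its purpose, an estimate of the additional benefit of CfD as well as its resource implications.

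**Working it through.** **Inputs.** Margin 2 PHQ-9 points, SD 6.9, one-sided 2.5%, power 90%, true difference 0 (Sample Size); 250 per arm (Abstract, Methods). An alternative true difference of −1.0 comes from the later service data set in the section on pilot work, where change was 7.3 points with CBT and 6.3 with counselling. Differences are CfD minus CBT, so negative values favour CBT.

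**The plan's own figure.** n per arm = 2 × [6.9 × (1.960 + 1.282) / 2]² ≈ 250.1, rounded up to 251, or 502 in total. The stated 500 is reproduced, and power at 250 per arm is 0.900. The sample size is not in question.

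**Cut-offs.** The article defines neither *equivalent* nor *more effective*. Assume, as the most favourable reading, that the first means non-inferior and the second means two-sided p<0.05.

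- SE = 6.9 × √(2/250) = 0.617; 95% half-width = 1.96 × 0.617 = 1.21.
- Non-inferior if the estimate exceeds −2 + 1.21 = −0.79.
- CBT better if the estimate is below −1.21; CfD better if it is above +1.21.
- Estimates from −1.21 to −0.79 fit neither branch. Those above +1.21 fit both, since CfD is then non-inferior and more effective.

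P(neither branch | d) = Φ((−0.79 − d)/0.617) − Φ((−1.21 − d)/0.617).

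| True difference d | Non-inferior | Neither branch | CBT better |
|---|---|---|---|
| 0 | 90.0% | 7.5% | 2.5% |
| −0.5 | 68.1% | 19.4% | 12.5% |
| −1.0 | 36.7% | 26.6% | 36.7% |

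At d = 0 the 90.0% splits into 87.5% that fits cost minimisation alone and 2.5% that fits both branches. So on the design assumption the costs-only analysis is the most likely outcome.

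**Sensitivity to the definition.** If *equivalent* means a 95% CI within ±2 (the +2 limit is an assumption), power to show it at 250 per arm and d = 0 is 2Φ(2/0.617 − 1.96) − 1 = 0.80, not 0.90. About 310 per arm would give 0.90. The share fitting neither branch becomes 15% at d = 0 and 27% at −1.0.

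**Sensitivity to the standard error.** The gap is 3.92 × SE − 2 wide, here 0.42 points. It closes at SE = 2/3.92 = 0.51. At 250 per arm that is an effective SD of 0.51/√(2/250) ≈ 5.7, or about 1 − (5.7/6.9)² ≈ 32% of variance explained by covariates. With 200 per arm (an assumption) the gap probability rises to 15% at d = 0 and 39% at −1.0.

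**What cost minimisation leaves out.** The documents give no QALY SD. For an assumed SD of 0.15 to 0.30, the 95% half-width of the QALY difference at 250 per arm is 1.96 × SD × √(2/250) = 0.026 to 0.053 QALY. The costs-only branch carries none of this.

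**The case against.** The strongest reply is that the article is a summary. Working definitions of *equivalent* and *more effective* could sit in a health-economics plan that is not shown, and the gap probabilities depend on definitions the article does not give. That stands as far as the figures go: they are conditional, vary with the definition and the achieved standard error, and are 7.5% at the planning assumption of zero difference. The −1.0 row needs similar care, because the pilot section adds that modality was not significant once number of sessions and type of ending were modelled. But the switching rule itself is fixed in the article. No definition of the terms makes a PHQ-9 result into evidence of a zero QALY difference.

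Three stronger readings are tempting and are not supported.

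- A reader might infer that the EQ-5D-5L data would go unused. The Secondary analysis section commits without condition to analysing EQ-5D-5L change to 6 and 12 months. The data are left out of the economic result in one branch, not discarded.
- A reader might infer that an inconclusive trial would have no economic analysis at all. The opening commitment to establish cost-effectiveness and the costing paragraph carry no condition of their own. What is missing is a statement of which method then applies.
- A reader might count as harm the trials that show non-inferiority with a point estimate favouring CBT. At a true difference of 0 such estimates arise by chance, and treating the PHQ-9 difference as zero would be correct. They say nothing about QALYs.

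**Conclusion.** The point holds in this form: the rule for choosing the economic method is wrong as written. It makes a costs-only analysis depend on an equivalence finding that the design does not test, and it removes the 12-month QALY difference and its uncertainty from the economic result in that branch. On the most favourable reading of the terms, this is the likely branch: non-inferiority has 90% probability if the true difference is 0.

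The article also leaves open which method applies to an inconclusive result. The probability of one is 7.5%, 19% or 27% at true differences of 0, −0.5 or −1.0. This assumes a normally distributed estimate, SD 6.9, 250 per arm, and the stated reading of the two terms. How much decision uncertainty is lost cannot be sized from the documents, because no QALY SD is given; the 0.026 to 0.053 range is illustrative. The non-inferiority test, its margin and the sample size are not affected.

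**What to change.** Remove the conditional choice of method from the Economic analysis section. State that the 12-month cost-per-QALY analysis already described there will be carried out whatever the PHQ-9 result, with joint uncertainty in costs and QALYs, and that the cost difference will be reported as one component of it. This removes the need to define *equivalent* and *more effective* for this purpose and covers the inconclusive case. How the joint uncertainty is displayed can be left to the analysts.

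The cost is a change of wording and a little more analysis. EQ-5D-5L and service-receipt data are already scheduled at baseline, 6 and 12 months (Secondary Outcome Measures), so no new data collection is needed. The sample size and primary clinical analysis stay as they are.

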### Process Analyses

To achieve a fuller understanding of patients’ experiences of CBT and CfD and how these impact of the course of treatment, we will carry out a programme of process studies using a defined sampling frame comprising cases of therapy non-completion and accounts of positive change (based on questionnaire returns and selective interviews); patient engagement, resilience and therapeutic alliance (based on a subsample of routinely collected tapes); and the phenomenon of sudden gains and deteriorations (based on routinely collected sessional PHQ-9 scores). We will also be investigating therapy non-completion and accounts of change through telephone or face-to-face interviews with consenting participants who have dropped out of therapy.

### Risk procedures and reporting of adverse events

We follow standard operating procedures in relation to assessing patient risk and reporting and acting upon serious adverse events. All associated research staff are trained in the recognition of and response to distress and risk. Written protocols are followed, based on the standard operating procedures of the Clinical Trials Research Unit (CTRU), which are consistent with the Trust procedures within which framework we work.

### Public and patient involvement panel

A panel of service users and people with lived experience—the Public and Patient Involvement (PPI) Panel—has been established to advise on the strategy, implementation and future analysis of the data. One of the grant holders is a person with lived experience. Members of the PPI panel have been co-opted onto the Trials Steering Committee as well as the Trials Management Group. The panel is informed by recent guidance on PPI involvement [61]. The PPI panel meets approximately every 4 months to discuss issues arising from the implementation of the trial. Views and suggestions are fed back into the TSC and TMG agendas as a standing item. The PPI involvement is being extended to include patients who have completed the trial and who are able to provide input and feedback on its potential benefits.

### Confidentiality

Names of participants on the consent forms are stored separately from data in locked filing cabinets and only accessible by named personnel. A separate key linking names to ID numbers used in data files is stored in a password-protected file on a secure server and only accessible by named personnel.

### Governance and oversight of the trial

A Trials Steering Committee (TSC) has been established with an independent Chair and comprises representatives from differing professional groups together with members of the research team. A Data Monitoring and Ethics Committee (DMEC) has been convened under an independent chair with statistical expertise together with two independent clinicians. A data analyst independent of the trial provides closed reports to the DMEC for scrutiny of adverse events and any trends in the outcomes that would suggest it to be unethical to continue the trial. The chair of the DMEC provides a closed report to the Chair of the TSC. Any decision to stop the trial rests with the independent members of the TSC. In addition, a Trial Management Group (TMG) has been established comprising the research team and key local personnel involved in the trial with the purpose of checking operational procedures. The TMG is chaired by the lead investigator. A site file is maintained and constantly updated with all associated documentation.

## Discussion

The PRaCTICED trial is a large-scale (and may be the only) randomised trial investigating the efficacy of CfD against CBT. Extensive evidence exists for the efficacy of CBT but the evidence for other psychological therapies lags behind. Determining the relative efficacy of other bona fide therapies is important for all stakeholders. The non-inferiority design adopts a realistic approach to such a comparison in the context of a pragmatic trial nested within an existing NHS IAPT service. Advantages of an embedded trial include having access to routinely collected outcome measures as well as the additional measures required specifically by the trial. The routinely collected data include weekly-administered outcome measures, including the primary outcome measure (PHQ-9). Not only does this increase the likely response rate in terms of the primary outcome, but it also provides the additional level of repeated weekly measurement on the primary outcome measure across the course of treatment. Hence, the data collection demand on trial patients is only proportionately greater than for non-trial patients receiving therapies within the routine IAPT service. Further additional advantages of the trial utilising a routine service lies in having access to larger number of therapists. While the exact total number will not be known until the trial is completed, the aspiration is to have in the region of 30 therapists in total delivering interventions in the trial. As such, this will provide a minimum level in order to be able to investigate therapist effects.

However, carrying out trials within routine service settings has considerable challenges. One specific challenge has been the scaling up of sufficient numbers of counsellors trained in the CfD model. Given the part-time nature of the profession, training has been slow. In addition, attempting to train all existing counsellors in the service assumed that they would all embrace the CfD model, an assumption that has had to be adjusted (unpublished observations: [name], [name], [name]). In terms of the availability of both interventions at GP surgeries, this has proved to be a challenge. However, the issue has been largely resolved by the addition of a central wait list resourced by available trial therapists [62]. At an organisational level, the requirement for prioritising and implementing a rigorous trial amidst the realities of an NHS IAPT service delivering therapies under ever-increasing national performance targets and annual cost efficiencies is a major challenge. This has necessitated generating innovative and flexible partnership models between the research team and service organisation. For example, a key decision has been the part-time secondment of a PWP working in the service to the trial research team, thereby enabling a highly effective link between the research team and both NHS services and IT systems [63].

On completion of data collection and subsequent analyses, the findings from the trial will make a significant contribution to the evidence base for Counselling for Depression as contrasted with CBT, which is considered the front-line psychological intervention for depression. As such, the findings will be of importance to all stakeholders, whether they are commissioners purchasing services, practitioners delivering therapies, or patients seeking a choice and receiving such interventions.

### Trial Status

The study commenced recruitment in October 2014 and patient recruitment is on-going.

## Abbreviations

BDI-II: Beck Depression Inventory II
CACE: Complier-adjusted causal effect
CBT: Cognitive behaviour therapy
CD-RISC: Connor-Davidson Resilience Scale
CfD: Counselling for depression
CIS-R: Clinical Interview Schedule-Revised
CORE-OM: Clinical Outcomes in Routine Evaluation-Outcome Measure
CSQ: Client Satisfaction Questionnaire
CSRI: Client Service Receipt Inventory
CTS-R: Cognitive Therapy Scale-Revised
EQ-5D-5L: Euroqol 5D-5L
GAD-7: Generalised Anxiety Disorder-7
IAPT: Improving Access to Psychological Therapies
ITT: Intention to treat
MINI: Mini International Neuropsychiatric Interview
NHS: National Health Service
PCEPS: Person-Centred and Experiential Psychotherapy Scale
PHQ-9: Patient Health Questionnaire-9
PP: Per-protocol
PPI: Public and patient involvement
PRaCTICED: Pragmatic Randomised Controlled Trial assessing the non-Inferiority of Counselling and its Effectiveness for Depression
SACS-CBT: Session Adherence and Competence Scale-CBT
SACS-CfD: Session Adherence and Competence Scale-CfD
WSAS: Work and Social Adjustment Scale
